#### Sample size calculation

2.2.2.

In order to stablish the sample size required for this trial, we follow recommendations by Bell et al. (2018) which proposed that a sample size of 60 participants would be adequate considering an effect size of 0.3 and 80% of power. Following this recommendation, our sample will be comprised of 60 participants, 20 in each baseline condition (6, 8 and 10 days of assessment before the intervention).

### Procedures

2.3.

A complete diagram of the procedures can be consulted in Figure 1. In the present investigation, all consecutive patients presenting post COVID-19 condition and symptoms of anxiety or depression are requested to participate. Participants will be recruited by medical staff collaborating in the project ARACOV-01 in three different centres (Lozano Blesa Clinical University Hospital, Zaragoza; Huesca Pirineos Health Centre, and Teruel Ensanche Health Centre) from Spain. An additional centre, namely the Royo Villanova Hospital from Zaragoza acts as a coordinator centre (author [name]). Specifically, nurses inform patients who cannot be included in the cohort “Specialized nutritional intervention and rehabilitative treatment for improvement of quality of life in a cohort of patients with post COVID-19 condition” about the possibility of being enrolled in the present trial “Efficacy of the Unified Protocol for Transdiagnostic Treatment of Emotional Disorders in People with Post COVID-19 Condition and Emotional Symptomatology.” The principal investigator from the transdiagnostic intervention cohort is from the Health Research Institute from Aragon and Zaragoza University ([name] author).

**Figure 1 fig1:**
[figure not shown]
Flow chart of participants and procedures.

Participants who meet the inclusion criteria (Table 1) will be given the information sheet and will sign the informed consent in the face-to-face consultation with the nursing team. Then, the psychologist of the study ([name]) will contact participants by telephone and will arrange an online session through a video-call to assess EDs according to the Anxiety and Related Disorders Interview Schedule for DSM-5 (ADIS-5; Brown and Barlow, 2014) which would also help to explore if any exclusion criteria are present (i.e., participants present a severe mental health issue or current suicidal ideation). Patients who meet any of these exclusion criteria will be recommended to consult with their mental health service of reference. If inclusion criteria are accomplished, participants will receive the pre-assessment protocol through e-mail and they will answer the questionnaires via the online platform Google Forms. Once the pre-assessment is completed, each participant will be sequentially and randomly assigned to one of the three multiple baseline conditions (Condition 1: 6 days of baseline assessments; Condition 2: 8 days of baseline assessments; Condition 3: 10 days of baseline assessments). During the baseline period, participants will receive daily e-mails with the online baseline assessment to be answered through Google Forms. Randomization to different baseline conditions will be conducted with a computer-generator online software (www.randomizer.org). An independent researched not involved in the implementation of the psychological intervention will sequentially assign participants to the three baseline conditions. Participants and professionals will know the baseline condition to which patients have been assigned.

### Outcomes

2.4.

The assessment protocol of the study includes nine assessment points (eligibility, baseline, pre-assessment, during treatment, post-assessment and four follow-ups). Table 2 shows the measures used in each phase of the study.

**Table 2 tab2:** Measures administration during the different phases of the trial.

Outcome	Eligibility	Pre	Baseline	Treatment	Post	Follow-ups
ADIS-5	X					
Sociodemographic	X					
COVID-19 symptoms	X					
OASIS		X	X	X	X	X
ODSIS		X	X	X	X	X
MEDI		X			X	X
EuroQol-5D		X			X	X
DERS		X			X	X
DTS		X			X	X
CSQ-8					X	
UP-satisfaction					X	

Pre, pre-assessment; Post, post-assessment; ADIS, anxiety and related disorders interview schedule for DSM-5; OASIS, overall anxiety severity and impairment scale; ODSIS, overall depression severity and impairment scale; MEDI, the multidimensional emotional disorder inventory; EuroQol-5D, health-related quality of life; DERS, difficulties in emotion regulation scale; DTS, distress tolerance scale; CSQ-8: client satisfaction questionnaire; UP: Unified Protocol.

#### Primary outcomes

2.4.1.

Sociodemographic: sex, age, place of residence, marital status, employment status, healthy habits (i.e., smoking, alcohol, physical activity, diet), SARS CoV 2 vaccination. Sociodemographic variables will be evaluated to characterize the sample.COVID-19 symptoms: symptoms of post COVID-19 condition referred by the patient according to 10 categories: General, respiratory, gastrointestinal, musculoskeletal, cutaneous, otolaryngological, neurological, cardiovascular, psychological and other symptoms. COVID-19 characteristics will be assessed to describe the sample.Overall Anxiety Severity and Impairment Scale (OASIS; Norman et al., 2006; Osma et al., 2021): it consists of 5 items assessing frequency of anxiety symptoms, severity of anxiety symptoms, avoidance and interference. Higher scores indicate more severe anxiety symptoms. Good internal consistency was found in the Spanish version of this instrument (α = 0.87; Osma et al., 2021).Overall Depression Severity and Impairment Scale (ODSIS; Bentley et al., 2014; Osma et al., 2021): it comprises 5 items assessing frequency of depressive symptoms, severity of depressive symptoms, anhedonia and interference. Higher scores represent more severe depressive symptoms. Excellent internal consistency was found in the Spanish version of this instrument (*α* = 0.94; Osma et al., 2021).Anxiety and Related Disorders Interview Schedule for DSM-5 (ADIS-5; Brown and Barlow, 2014): it is a structured clinical interview to diagnose current anxiety, mood and related disorders (i.e., obsessive-compulsive, trauma, somatic symptoms, substance use) according to the Diagnostic and Statistical Manual of Mental Disorders criteria (5th edition, DSM-5; American Psychiatric Association, 2013). Different editions of the ADIS have shown good reliability with good-to-excellent interrater agreement for DSM disorders (Brown and Barlow, 2014). In this trial, this interview will be used to assess eligibility criteria to participate in the trial.Adjustment disorders: adjustment disorders are usually accompanied by medical illness (American Psychiatric Association, 2013). Given the high prevalence of adjustment disorders in the context of the COVID-19 pandemic, and specially in people who experience COVID-19 stressful situations (Ben-Ezra et al., 2021), participants in this trial will be assessed for the presence of adjustment disorders according to DSM-5 criteria (American Psychiatric Association, 2013).

#### Secondary outcomes

2.4.2.

The Multidimensional Emotional Disorder Inventory (MEDI; Rosellini and Brown, 2019; Osma et al., 2021): it is composed of 49 items that allow the assessment of nine dimensions of the EDs to obtain a transdiagnostic profile. Proposed dimensions include: neurotic temperament, positive temperament, depressed mood, autonomic arousal, somatic anxiety, social anxiety, intrusive cognitions, traumatic re-experiencing and avoidance. Excellent internal consistency was found in the Spanish validation (0.74 ≥ *α* ≤ 0.92; Osma et al., 2021).Health-related quality of life (EuroQol-5D; Brooks, 1996; Herdman et al., 2001): it has four different components. In this study, two components were used to collect information about health-related quality of life. The first one consists of 5 items that assess health state on five different domains (i.e., mobility, self-care, usual activities, pain/discomfort and anxiety/depression). The second component evaluates subjective health state on a thermometer (0–100). Higher scores indicate higher quality of life. This instrument has shown good convergent and construct validity in the Spanish version (see Badia et al., 1998)Difficulties in Emotion Regulation Scale (DERS; Gratz and Roemer, 2004; Hervás and Jódar, 2008): it is composed of 28 items assessing difficulties in the regulation of emotions when facing distress. It includes 5 dimensions: inattention, confusion, rejection, interference and lack of control over emotions. Higher scores represent more difficulties in the regulation of emotions. Good internal consistency was found in the Spanish version of this instrument (*α* = 0.74; Hervás and Jódar, 2008)Distress Tolerance Scale (DTS; Simons and Gaher, 2005; Sandín et al., 2017): it consists of 15 items which assess distressful psychological states. It can be divided in four subscales: perceived ability to tolerate emotional distress, subjective appraisal of distress, attention absorber by negative emotions and regulation efforts to alleviate distress. Lower scores indicate greater ability to tolerate distress. Good internal consistency was found in the Spanish validation (0.83 ≥ *α* ≤ 0.89; Sandín et al., 2017).Adaptation of Client Satisfaction Questionnaire (CSQ-8; Larsen et al., 1979): the original version of the CSQ-8 comprises 8 items which assess general satisfaction with services. In our adaptation, 6 of these 8 items were maintained: perceived quality, meeting expectations, recommendation to family or friends, perceived utility of the learned techniques, general satisfaction with the intervention and desire to participate in this kind of intervention in the future. An additional question was included in order to assess discomfort generated by the intervention. The Likert response scale was changed from 4 points (0 = “No, definitely no” – 4 = “Yes, definitely”) to 11-points Likert scale (0 = “Bad/nothing” – 10 = “Excellent/very much”). Finally, to explore the qualitative opinion of participants, five open questions were added: (1) Would you like to include other content that was not addressed in this psychological program? (2) Do you think there is any unnecessary content in this program that you would remove? (3) Do you feel the program duration (8 sessions of 1 h each) is sufficient? (4) How satisfied are you with the format of the program (online and individual)? (5) Please use this space to express any concerns you may have with regard to the program. The original version of the CSQ-8 showed excellent internal reliability (*α* = 0.92; Larsen et al., 1979).Evaluation questionnaire of the UP modules: an *ad hoc* questionnaire with 7 items was developed to assess patients’ satisfaction with the psychological programs received. The first question assesses the general perceived utility of the program to improve emotion regulation skills. The remaining 6 questions assess the perceived utility of the program to improve the six abilities that are trained during the UP psychological intervention. Each item is answered using a scale from 0 = “Nothing” to 10 = “Very much,” higher scores indicate greater satisfaction with the UP.Baseline assessment: OASIS and ODSIS will be administered daily during baseline and weekly during the treatment phase as a measure of change. Temporality of questions will be changed during baseline to assess anxiety and depressive symptoms during the previous day instead of “during the last week.”

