### Design

2.1.

This protocol describes the procedures of a pilot study which uses multiple baseline single case design to explore the preliminary clinical utility and acceptability of the UP in the treatment of EDs or symptoms in a sample of patients with post COVID-19 condition. This trial has been previously registered in clinicaltrials.gov on October 14th, 2022 and updated on January 20th, 2023 (NCT05581277). The present protocol follows the SPENT checklist (SPIRIT extension for N-of-1 trials; Porcino et al., 2020) that can be consulted in Supplementary material A (SPENT checklist) and B (abstract checklist).

Multiple baseline single case design is frequently used in clinical settings to explore the effect of an intervention on a reduced group of patients (Kazdin, 2011). It is selected for this trial as no control group is needed because each participant acts as their own control comparison (Kratochwill et al., 2012). Current guidelines recommend three different baseline conditions with at least 3–5 data points in each group (Kratochwill et al., 2010, 2012). Accordingly, we will assign participants to three different baseline conditions: 6, 8 and 10 days of assessments prior to the beginning of the intervention. Participants will by randomly allocated to one of the three baseline conditions.

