### Data analysis

2.6.

The Statistical Package for the Social Sciences (SPSS) version 22.0 for windows (IBM Corp, 2013) will be used to conduct the statistical analysis.

First, normal distribution test will be conducted to explore whether the data obtained followed a normal distribution. According to the distribution of the sample, we will use parametric or non-parametric analyses. Then, descriptive data (mean, standard deviation, and proportions) of all study variables will be reported in order to characterize the sample (i.e., sociodemographic and psychosocial status). Missing-value analysis and the Little Missing Completely At Random test (MCAR) will be used to check whether missing values are randomly presented. Last observation carried forward (LOCF) will be used in this case (Jakobsen et al., 2017).

Analysis of Variance (ANOVA), or its equivalent non-parametric Friedman test, will serve to test whether there are differences between the three baseline conditions at pre-assessment to ensure that randomization resulted in comparable groups. Repeated measures ANOVA will help to determine if between-group (differences in outcome variables between the three baseline conditions at different assessment points) and within group differences (differences between the pre-treatment and the remaining assessments in the outcome variables for each baseline condition) are present. Additionally, effect sizes (Cohen’s *d*) will be calculated for both between and within group analyses. Effect sizes will be interpreted as small (*d* ≈ 0.2), medium (*d* ≈ 0.5) or large (*d* ≈ 0.8).

As recommended for n-of-1 trials, visual analysis of the data by graphs will also be used to determine whether the psychological outcomes improve as a consequence of intervention contents. By doing so, we will establish the baseline pattern on OASIS and ODSIS scales and compare it with the data within the following treatment phase and also with results obtained during the follow-up assessments. The statistical Software R version 4.1.0 (R Core Team, 2021) will be used for the graphical representation of slopes.

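### OASIS and ODSIS switch from previous-day to (by the natural reading) last-week recall at each participant's treatment start, so the visual baseline-versus-treatment comparison cannot separate therapy from a change of instrument

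*Protocol article*

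**What the plan says.** The OASIS and ODSIS schedule is in the last entry of Section 2.4.2: "OASIS and ODSIS will be administered daily during baseline and weekly during the treatment phase as a measure of change". The same entry adds: "Temporality of questions will be changed during baseline to assess anxiety and depressive symptoms during the previous day", and gives last-week wording as what is being replaced. No similar change is described for any other time point. Table 2 lists both scales at pre-assessment, baseline, treatment, post-assessment and follow-ups.

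Section 2.6 says how the series will be used: "we will establish the baseline pattern on OASIS and ODSIS scales and compare it with the data within the following treatment phase", and also with the follow-up results. The purpose of this graphical analysis is to "determine whether the psychological outcomes improve as a consequence of intervention contents". Section 2.1 gives the reason for having no comparator: "no control group is needed because each participant acts as their own control comparison". Section 2.3 gives the stagger: "Condition 1: 6 days of baseline assessments; Condition 2: 8 days of baseline assessments; Condition 3: 10 days of baseline assessments". It places the pre-assessment before randomisation and before the daily series.

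The formal test in Section 2.6 is a repeated-measures ANOVA of pre-treatment against the remaining assessments. The limitations in Section 3 do not mention the change of wording.

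**The concern.** A multiple-baseline design supports a causal reading only if the same thing is measured in the same way on both sides of the phase change. Here the wording changes exactly at that point. Section 2.4.1 says the items cover frequency, severity, avoidance or anhedonia, and interference. A person need not answer such items alike for one day and for seven: a single day can be free of anxiety in a week that was not, and single-day scores can vary more than a weekly summary.

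A step in level or a change in scatter at treatment start could then be read as benefit with no true change, or could conceal a true change. At stake is the part of the analysis that lets participants act as their own controls, on the two scales that measure the primary outcomes. Once the data are collected, no analysis of these two series alone can undo the problem.

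**Working it through.** The plan gives no figure for this point, so there is none to reproduce. The check is whether the planned data can separate a phase effect from a recall-window effect.

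**Inputs.** Baselines of 6, 8 and 10 daily ratings (Sections 2.1 and 2.3); weekly ratings in treatment (Section 2.4.2); one last-week rating at pre-assessment (Section 2.3, Table 2). Assumptions: 8 treatment ratings, one per session; last-week wording in treatment.

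**Step 1: the two series that are compared.** Take one participant per baseline condition. Model: score = person intercept (3 columns) + linear time + phase (0 baseline, 1 treatment) + window (0 previous day, 1 last week), 6 columns in all. There are 6 + 8 + 10 = 24 baseline rows with phase = window = 0, and 3 × 8 = 24 treatment rows with phase = window = 1. The phase and window columns are identical, so their correlation is 1.00 and the rank is 5 of 6. The stagger does not help, because the window switches at each person's own phase change. Without the window term, which would be the case if wording were the same in both phases, the model has 5 columns and rank 5.

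**Step 2: adding the pre-assessment.** This adds 3 rows with phase = 0 and window = 1. The rank rises to 6. The phase–window correlation is (24 × 24 − 0 × 3) / √(24 × 27 × 27 × 24) = 576 / 648 = 0.89. Separation would then rest on one rating per person and an assumed linear trend, and Section 2.6 does not use that rating as a bridge.

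**Step 3: the stagger.** The longest and shortest baselines differ by 10 − 6 = 4 days. The article does not say when session 1 or the first weekly rating falls.
- If session 1 is the day after baseline (days 7, 9, 11) and the first rating comes a week later (days 14, 16, 18), the first treatment rating in the 6-day group comes after the 10-day group's last baseline day (14 > 10). There are then no concurrent treated and untreated ratings.
- If ratings start at session 1, the 6-day group is rated on day 7 while the others are still in baseline, but its last-week window covers baseline days.
- If the 6-day group is rated on day 10, the preceding seven days are days 3 to 9, of which days 3 to 6 (4 of 7) are untreated.

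**Step 4: illustration only.** Suppose therapy has no effect and the wording change shifts scores by δ SD of the within-person difference. A pooled paired t-test with n = 60 and two-sided 5% has noncentrality δ√60 on 59 degrees of freedom. The chance of a significant result in the direction of the artefact is:

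| δ (assumed) | δ√60 | Probability |
|---|---|---|
| 0.1 | 0.77 | 0.12 |
| 0.2 | 1.55 | 0.33 |
| 0.3 | 2.32 | 0.63 |
| 0.5 | 3.87 | 0.97 |

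The article gives no value for δ, and the plan contains no such test.

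**The case against.** The strongest reply is that the hypotheses in Section 1 concern improvement from pre- to post-assessment and its maintenance at follow-up. Those contrasts appear to use last-week wording throughout, so a reader who inferred that all the efficacy results are confounded would go too far. This stands, provided that pre-treatment in Section 2.6 means the pre-assessment. But such a contrast has no control for natural recovery or regression to the mean, so it does not replace the phase comparison.

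Second, the probabilities in the table might be read as the trial's false-positive rate. They are not: the phase comparison is visual, no pooled paired test is planned, and the shifts are assumed.

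Third, a reader might infer that treated and still-untreated participants are never rated at the same time. That holds only under one unstated schedule. Under others there is overlap, although the rating then looks back into baseline days.

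Fourth, a single shift in wording cannot by itself produce a progressive fall across the weekly ratings. This is also right. A gradual decline within treatment would not be explained by the artefact, although it would still need a comparable baseline trend to support attribution.

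Finally, previous-day recall suits daily rating, since last-week wording asked every day would overlap heavily; the article discloses the change, and the study is a pilot. These points justify the daily wording in baseline. They do not explain why that wording is dropped when treatment starts.

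**Conclusion.** The point holds for the visual baseline-versus-treatment and baseline-versus-follow-up comparisons. As written, recall window and phase are fully aliased in the two series compared in each participant, and neither the stagger nor the pre-assessment as used resolves this. A step in level or variability at treatment start therefore cannot be assigned to the intervention with confidence, and the absence of a step cannot be taken as no effect. The size and direction of the artefact cannot be derived from the article.

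The conclusion rests on one inference, that treatment and follow-up keep last-week wording. That is the natural reading of a change confined to baseline, and nothing in the article contradicts it. The weakness of the stagger is a secondary point that depends on the unstated timing of sessions and ratings.

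**What to change.** Add the previous-day OASIS and ODSIS (5 items each, 10 in all) to every weekly treatment rating and to the post and follow-up assessments. State in Section 2.6 that baseline-versus-treatment and baseline-versus-follow-up graphs use previous-day scores only, and that last-week scores serve the pre, post and follow-up contrasts. Say there that pre-treatment means the pre-assessment, if that is intended, and state when session 1 and the first weekly rating fall.

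The cost is 10 short items per occasion. With 8 treatment ratings (assumed), one post-assessment and four follow-ups, that is 13 × 10 = 130 extra items per participant over the whole study. The form and the online route already exist. The downside is a small added burden on patients who already have symptoms. The sampling interval would still differ between phases, but each plotted score would have the same recall period.

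Continuing daily ratings for two weeks into treatment is not needed. With session 1 the day after baseline, it would give about four days of overlap (days 7 to 10) between the 6-day and 10-day groups. If sessions are weekly, only the first, goal-setting session in Table 3 would have been delivered by then.
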